# Akwenda intervention programme for children and youth with cerebral palsy in a low-resource setting in sub-Saharan Africa: protocol for a quasi-randomised controlled study

**DOI:** 10.1136/bmjopen-2020-047634

**Published:** 2021-03-08

**Keywords:** developmental neurology & neurodisability, rehabilitation medicine, community child health

## Abstract

**Introduction:**

Cerebral palsy (CP) is the most common childhood-onset motor disorder accompanied by associated impairments, placing a heavy burden on families and health systems. Most children with CP live in low/middle-income countries with little access to rehabilitation services. This study will evaluate the Akwenda CP programme, a multidimensional intervention designed for low-resource settings and aiming at improving: (1) participation, motor function and daily activities for children with CP; (2) quality of life, stress and knowledge for caregivers; and (3) knowledge and attitudes towards children with CP in the communities.

**Methods:**

This quasi-randomised controlled clinical study will recruit children and youth with CP aged 2–23 years in a rural area of Uganda. Children will be allocated to one of two groups with at least 44 children in each group. Groups will be matched for age, sex and motor impairment. The intervention arm will receive a comprehensive, multidimensional programme over a period of 11 months comprising (1) caregiver-led training workshops, (2) therapist-led practical group sessions, (3) provision of technical assistive devices, (4) goal-directed training and (5) community communication and advocacy. The other group will receive usual care. The outcome of the intervention will be assessed before and after the intervention and will be measured at three levels: (1) child, (2) caregiver and (3) community. Standard analysis methods for randomised controlled trial will be used to compare groups. Retention of effects will be examined at 12-month follow-up.

**Ethics and dissemination:**

The study has been approved by the Uganda National Council for Science and Technology (SS 5173) and registered in accordance with WHO and ICMJE standards. Written informed consent will be obtained from caregivers. Results will be disseminated among participants and stakeholders through public engagement events, scientific reports and conference presentations.

**Trial registration number:**

Pan African Clinical Trials Registry (PACTR202011738099314) Pre-results.

Strengths and limitations of this studyThis is the first registered randomised controlled clinical trial of a comprehensive, multidimensional intervention programme for children over the age of 2 years and youth with cerebral palsy in a low-income and middle-income country.The core of the programme is based on principles derived from the International Classification of Functioning, Disability and Health (ICF), evidence-based interventions and universal health coverage.The study will address several ICF categories and include a battery of objective, validated and adapted outcome measures that will measure a broad spectrum of intervention outcomes at the level of the child, the caregiver and the community.The small sample size will make it difficult to identify small effects and it will not be possible to identify which of the components is most effective.

## Introduction

Cerebral palsy (CP) is a life-long motor disorder due to non-progressive disturbances of the developing fetal or infant brain.^1^ In addition to gross and fine motor impairments, children with CP often have associated impairments in hearing, vision, cognition and communication, as well as behavioural problems and seizures. Feeding difficulties result in a high prevalence of malnutrition.^2^ Apart from access to mainstream healthcare, social services and education, children with CP require services for their special needs. These needs are not met in many low/middle-income countries (LMICs) where children with developmental disabilities often are neglected by primary healthcare and education services and face discrimination and exclusion.^3 4^ Discrimination often stems from a lack of knowledge, prejudice and cultural norms, which in turn lead to stigma and entrenched social exclusion.^5–7^ LMICs are characterised by a paucity of health professionals specialised in childhood disability including physiotherapists, occupational, and speech and language therapists,^8–10^ as well as a lack of assistive devices.^11^ Professional consensus reports from Africa illustrate an immense lack of services for children with neurodevelopmental disorders with limited health worker and caregiver awareness, poor community attitudes and practices, lack of health worker training, unclear treatment or referral guidelines, and a lack of diagnostic facilities or feasible health interventions.^12–14^

The scarcity of rehabilitation services has resulted in families being left alone to care for the child with CP, neither knowing the cause and the life-long prognosis, nor given any advice on how to best care for the child. This situation contributes to the high risk for stress, isolation, depression and reduced quality of life for the caregivers.^15–18^ In the absence of health professionals, training of family members has become a strategy to address the workforce gap, for example, the Caregiver Skills Training programmes for children with developmental delays and disabilities.^19^ A recent initiative for CP in LMICs is a caregiver training package delivered by health workers (Getting to know cerebral palsy),^20^ which aims to empower caregivers and improve care and support for children, recently studied in Ghana.^21 22^ A comprehensive parent-delivered intervention programme for early intervention for infants at high risk to develop CP due to adverse events at birth or shortly after, (Learning through Everyday Activities with Parents; LEAP_CP) is currently being evaluated in a randomised controlled trial in Bangladesh.^23^ In addition to parent education, LEAP_CP comprises goal-directed motor and cognitive skills training and strategies to enrich the home environment. Another early intervention parent-delivered programme, the ‘ABAaNA EIP’ is currently being trialled in Uganda for infants under 12 months.^24^ It comprises 1 home visit and 10 modules delivered by trained expert parents to groups of 6–10 families of infants once every 1–2 weeks over a 6-month period. There are thus several emerging intervention programmes for at-risk infants and young children with CP in low-resource settings based on evidence derived from high-income countries (HICs). However, as yet, there is no evidence-based programme nor a programme targeting children over 2 years of age in LMICs.

The neglect and lack of services and support for children with CP in LMICs are underscored by limited information about the epidemiology of CP in these countries. In 2015, our research team published the first population-based study on children with CP in sub-Saharan Africa, reporting a 50% higher prevalence than HICs (a crude prevalence of 3.1/1000,^25^ vs 1.8–2.3 in HICs.)^26–29^ The finding of a higher prevalence of CP has been confirmed in a recent community-based key informant study from Bangladesh^30 31^ and is consistent with some previous estimates from different LMIC populations.^32–35^ Many children in our study had severe motor impairments often in combination with intellectual disability, impairments in communication and seizures. None had received regular rehabilitation services. Only 8% of those unable to walk had wheelchairs, and none had assistive devices for walking, hearing, seeing or communication. Only one-third of the children attended school. Notably, the Ugandan cohort of children with CP exhibited significantly lower developmental trajectories of mobility and self-care skills when compared with a similar CP cohort of Swedish children. We concluded that the needs for children with CP and their families in rural Uganda were not met, illustrated by the scarcity of health services, assistive devices and low school attendance, and that the absence of interventions and support contributed to the poorer development of mobility and self-care skills.^4^

To address this unsettling situation, we have developed a comprehensive and holistic intervention programme for children with CP living in rural, low-resource settings, which we plan to implement and evaluate in this cohort of children with CP in rural Uganda. This Akwenda CP programme was developed by an international team of experts on CP and rehabilitation, an academic team from Uganda, a team from Malamulele Onward in South Africa, and a local team of therapists and social workers living in the region in a three-step process described in online supplemental file 1. The first step involved identifying key principles based on current concepts of disability, rehabilitation and interventions for children with CP. In the second step, the team set up three general programme goals based on the principles and needs of children with CP and their families, which had been identified in previous studies.^2 4 25 36^ In the third step, the team developed the Akwenda CP programme that comprises five components, based on the principles and aimed at achieving the goals formulated in the previous steps (see online supplemental figure 1 and online supplemental tables 1 and 2).

10.1136/bmjopen-2020-047634.supp1Supplementary data

### Aims and hypotheses

This protocol describes the method and implementation of the Akwenda CP programme study, which aims to evaluate the programme’s feasibility and impact on children, caregivers and society. The specific aims are to:

Determine the efficacy of the intervention on the motor function, daily activities and participation of children with CP.Hypothesis 1: children with CP receiving the intervention will improve their motor function, enhance their activity and increase their level of participation compared with children receiving usual care.Describe the impact of the intervention on the behaviour and mental health of caregivers of children with CP.Hypothesis 2: caregivers of children with CP receiving intervention will have a better quality of life, reduced levels of anxiety and stress, and increased levels of knowledge and practical caregiver competence compared with caregivers receiving usual care.Determine the impact of the intervention on the community awareness of childhood disability and attitudes towards children with disability and their families.Hypothesis 3: stakeholders, teachers, health professionals and the lay community will have increased their knowledge about childhood disability and the barriers limiting their participation in society. Their perception of disability will become more positive.

## Methods

### Study design

The project is designed as a quasi-randomised controlled clinical study conducted according to the Standard Protocol Items: Recommendations for Interventional Trials guidelines (see figure 1). Children with confirmed diagnoses of CP will be assigned to either a study group or control group, based on geographical regions. The study group will receive the Akwenda CP programme during the first year, while the control group will be on a waitlist and receive usual care. The control group will receive the intervention after 1 year. Children and caregivers of the first intervention group will be encouraged to continue with the parent-led workshops and to implement new caregiving skills and behaviours during the second year. Both groups will be assessed prior to the start of the intervention, after 1 year and after 2 years.

**Figure 1 F1:**
[figure not shown]
Flow chart for children in the Akwenda Cerebral Palsy (CP) Intervention Study. C&A, communication and advocacy; CFCS, Communication Function Classification System; GAS, Goal Attainment Scale; GMFCS, Gross Motor Function Classification System; GMFM-66, Gross Motor Function Measure; MACS, Manual Ability Classification System; PEDI-UG, Uganda version of Pediatric Evaluation of Disability Inventory; PedsQL, Pediatric Quality of Life Inventory; PMP, Picture my Participation; TAD, technical assistive device; ZCCS, Zimbabwe Caregiver Challenges Scale.

### Study site

The study will be performed at the Iganga/Mayuge Health Demographic Surveillance Site (IM-HDSS), which was set up in collaboration between Makerere University and Karolinska Institutet. It comprises 65 villages including 15 964 households, and >85 000 individuals of whom approximately 50% are under 18 years. The populations are predominantly rural subsistence farmers living under the poverty level, but 20% of the population resides in the semiurban Iganga town. The HDSS includes 1 general hospital (Iganga Hospital), 27 health centres and 132 private health providers.

### Participants and recruitment

Participants will be from a population-based cohort of children with CP identified from previous screening carried out at IM-HDSS in 2015 using the definition of CP Surveillance in Europe.^25 37^ In addition, children with CP aged 2–6 years living in the same area will be recruited by the community development officer. The CP diagnosis will be confirmed by a child neurologist using the same definitions. Hence, the study population will be between 2 and 23 years at the onset of the intervention study.

### Randomisation and blinding

Since the community and advocacy intervention will target the community, all children from a particular village need to be in the same group. Children will thus be allocated to groups depending on the village where they reside. Neighbouring villages will be clustered together to reduce contamination between groups resulting in two geographically defined groups, which will be matched for age, sex and motor function. The decision regarding which group will receive the intervention first will be decided by a coin flip. A team of therapists and a social worker will administer the assessments and surveys before the study to capture background and baseline data. A group of independent therapists, not involved in the intervention, will administer the outcome measures after the interventions. These examiners will be blinded to group allocation.

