### Sample size

From the initial cohort of 97 children with CP, 82 children had survived.^36^ In order to include younger children, we have identified 20 additional children with CP living in the area. From these two samples, 88 children will be recruited to form two comparable groups each with 44 children. In addition, the primary caregiver of each child will be included in the two arms, and 40 community representatives will be included in the intervention arm for evaluation of the C&A component.

To explore whether this sample size was sufficient for detecting a true effect of the intervention, we did power calculations to determine what mean difference in Pediatric Quality of Life Inventory (Peds-QL; primary outcome measure for caregivers) scores was needed between arms. We used a Peds-QL mean of 12.5 and SD of 18.6, from a previous study in Ghana on caregivers of children with CP.^22^ In our population with 44 per group allowing for a 10% non-participation at follow-up, a mean difference of at least 12.5 points between groups is needed for 80% power and a type I error of 0.05. Considering that the mean improvement after a parent training intervention in Ghana in Peds-QL was +31.3 (95% CI 25.6 to 37.0), this seems plausible.^22^

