#### Data management and analysis

Data will be collected in Open Data Kit using tablets, and electronic data will be managed through a secure database. The use of electronic data collection with built-in quality control will minimise missing or inaccurately entered data. The researchers will supervise data collection and monitor the database in real time to address any quality issues that might be arising. Data will be analysed using Stata version 14.2. Standard analysis methods for a randomised controlled trial, including general linear mixed models, will be used to make comparisons between the intervention group and the waitlist group on an intention-to-treat basis. Effect estimate will be presented as a mean difference and 95% CI. Secondary outcome analyses will use similar methods to compare all other outcomes between groups immediately post-intervention and again 1 year later. The GAS goal attainment scores for the intervention group will be analysed with paired t-tests on a within-group basis. A senior statistician will guide and assist with the analysis.

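### Each arm is a single geographical region assigned by one coin flip, so region cannot be separated from treatment, yet the article claims randomised-trial status, inference and power without this caveat

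*Protocol article*

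**What the plan says.** Under Study design, children "will be assigned to either a study group or control group, based on geographical regions". Randomisation and blinding gives the mechanism. The community component needs every child in a village to be in the same arm, so "Children will thus be allocated to groups depending on the village where they reside". Then "Neighbouring villages will be clustered together to reduce contamination between groups resulting in two geographically defined groups". These two groups are to be matched for age, sex and motor function. The only random step is the last one: "The decision regarding which group will receive the intervention first will be decided by a coin flip".

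Under Sample size, "88 children will be recruited to form two comparable groups each with 44 children". That section gives a detectable PedsQL difference of 12.5 points with 80% power and a type I error of 0.05, using SD 18.6 and 10% loss. It makes no allowance for a regional difference.

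Data management and analysis says: "Standard analysis methods for a randomised controlled trial, including general linear mixed models, will be used to make comparisons". Results are to be given as a mean difference with a 95% CI.

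The title, the abstract and Study design all call the study quasi-randomised. The strengths and limitations box drops that qualifier and presents the study as the first registered randomised controlled trial of its kind. The limitations listed there are the small sample and the inseparable programme components. Region confounding is not among them.

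**The concern.** With one region per arm, arm and region are the same variable. Anything that differs between the two areas, is not measured on the child or caregiver, and affects the outcome enters the estimated treatment effect. So does anything that happens in only one area during the year. The coin flip makes the sign of such a difference random but does not average it out, because there is only one unit on each side.

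The site description gives some reason to expect differences: "20% of the population resides in the semiurban Iganga town", while the rest is predominantly rural. The standard care section describes outside therapy as occasional and device donations as unpredictable.

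At stake are the between-arm tests of hypotheses 1 and 2. A reader who takes the stated error rate, CI and power at face value would credit them with a precision that the allocation cannot deliver.

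**Working it through.** **What the allocation fixes.** There are two allocated units, one per arm, so between-region degrees of freedom are 2 − 2 = 0. Two allocations are possible, so the smallest one-sided p-value from a re-randomisation test is 1/2. A village random effect absorbs correlation within villages. It says nothing about a region-level difference, because all villages in an arm share the same region.

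**The plan's own figure.** Inputs from Sample size: SD 18.6, 44 per arm, 10% loss (44 × 0.9 = 39.6, taken as 40), 80% power, alpha 0.05 (two-sided assumed). The detectable difference is 18.6 × (1.960 + 0.842) × √(2/40) = 11.65 points, against 12.5 stated. The stated value errs on the safe side. It corresponds to a design effect of about 1.14, which with about 40 per arm covers a region ICC of only (1.14 − 1)/39 ≈ 0.004.

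**Power at 12.5 points with a region effect.** The documents give no region ICC (ρ), so a range is assumed. The SE of the difference is 18.6 × √(2 × [1 + 39ρ]/40). Power is shown as if the region variance were known, which it cannot be.

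| ρ | SE | Power at 12.5 |
|---|---|---|
| 0 | 4.16 | 85% |
| 0.01 | 4.90 | 72% |
| 0.02 | 5.55 | 62% |
| 0.05 | 7.14 | 42% |

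**Type I error, unadjusted.** An unadjusted two-sample test estimates its SD within arms, which excludes the region component. The ratio of true to assumed variance is 1 + 40ρ/(1 − ρ), and the actual error is 2 × [1 − Φ(1.96/√ratio)].

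| ρ | Variance ratio | Factor on CI width (√ratio) | Error, formula | Error, simulation |
|---|---|---|---|---|
| 0.01 | 1.40 | 1.18 | 9.8% | 9.8% |
| 0.02 | 1.82 | 1.35 | 14.6% | 14.3% |
| 0.05 | 3.11 | 1.76 | 26.6% | 26.1% |

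Put another way, a fixed regional difference of 4 PedsQL points unrelated to treatment gives rejection in 16% of trials, since 4/4.16 = 0.96 standard errors. A difference of 6 points gives 30%.

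**Type I error, baseline-adjusted.** Both primary outcomes are measured at baseline. If the region effect is the same at baseline and follow-up, and the within-region baseline-outcome correlation is r (assumed), the ratio becomes about 1 + [40ρ/(1 − ρ)] × (1 − r)/(1 + r). At ρ = 0.05 and r = 0.5 this is 1 + 2.105/3 = 1.70. The formula then gives about 13%. Simulation gives slightly less, because the fitted SE also grows with baseline imbalance.

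| r | ρ = 0.01 | ρ = 0.02 | ρ = 0.05 |
|---|---|---|---|
| 0.5 | 6.5% | 8.3% | 12.2% |
| 0.7 | 5.6% | 6.7% | 9.1% |

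These are simulated rejection rates with 40 per arm. A change-score test stays near 5% under the same assumption. Neither analysis removes a trend or event confined to one region, which would add to these figures.

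**The case against.** The strongest reply is that the design is a reasoned trade-off, openly described. A community-level programme with meetings and radio talk shows needs whole villages in one arm, and two contiguous areas keep contamination low. The mechanism is stated in full, and the title, abstract and Study design all say quasi-randomised. That stands. A reader might infer that the article passes the study off as a randomised trial throughout. It does not: the label is wrong in the strengths box, and the randomised-trial framing of the analysis goes further than the allocation allows.

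A second reply is that mixed models are planned and their random effects belong in an analysis plan that is not shown. That also stands, so the absence of a stated village term is not part of this point. It does not answer the point either, because no choice of random effects separates region from arm here.

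A third reply is that baseline measurement limits the damage. It does for stable differences, as the last table shows. A reader might take 10% to 26% as the error rate of the planned analysis. The documents do not support that, because those rates belong to an unadjusted comparison.

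Finally, a reader might infer that schooling, care seeking and outside support are all wholly confounded with treatment. The documents do not say how these are distributed between the two areas. School attendance, care seeking and device use are recorded for each child before allocation and can be adjusted for. Only unmeasured regional factors and region-specific changes are inseparable from treatment.

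**Conclusion.** The point holds as a mismatch between design and claim. One region per arm follows directly from the text and does not depend on any assumed number. The stated 0.05 error, 95% CI and 80% power are valid only if there is no region effect on the analysed outcome, and the article does not say so.

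The size is uncertain. For an assumed region ICC of 0.01 to 0.05 with 40 analysed per arm, the error is about 10% to 26% unadjusted. It is about 5.5% to 12% with baseline adjustment, a stable region effect and a baseline-outcome correlation of 0.5 to 0.7. Region-specific trends over the year would raise the adjusted figures by an amount that the data cannot reveal. An analysis plan that is not shown could refine the model, but it could not supply the missing replication of regions.

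**What to change.** If the two-region split stays, three passages need rewording:

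- **Strengths and limitations.** Replace the randomised-trial claim with a quasi-randomised two-area controlled comparison, one area per arm. Add confounding by region as a limitation.
- **Data management and analysis.** Replace the reference to standard randomised-trial methods with baseline-adjusted mixed models. State that p-values and CIs are conditional on no region effect. Add a sensitivity table that widens the CI for a region ICC of 0.01 to 0.05. With ρ taken as the between-region share of the residual variance in the analysed outcome, the width factor is √(1 + mρ/(1 − ρ)). With 40 per arm this is about 1.18, 1.35 and 1.76 at 0.01, 0.02 and 0.05.
- **Sample size.** State that the 80% power and 0.05 error assume a region ICC of zero.

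A random intercept for the allocated block with Kenward-Roger degrees of freedom should not be offered as a remedy. With one block per arm it cannot be estimated apart from treatment.

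The cost is a few sentences and one small table, with no new data. If allocation has not yet been done, randomising several contiguous village blocks per arm is an option to consider, since the site has 65 villages. It would replicate regions within arms, at the price of more borders between arms and more contamination risk, so it is a trade-off for the team to weigh.

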### Data collection, management and analysis

#### Organisation and management

The Akwenda CP programme is a study within the CURIE research consortium, a collaboration between the Makerere University College of Health Sciences, Kampala, Uganda and Karolinska Institutet, Stockholm, Sweden, and clinical researchers from South Africa and the USA. The project will be guided by a steering group ensuring the conduct and coordination of the study. There will be a local Site Steering Committee consisting of the principal investigator (PI) ([name]), an administrative project manager, a PhD student and a parent carer. The project manager will be coordinating the study on site and report to the PI.

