#### Data collection and monitoring

Two therapists not involved in the intervention will administer the baseline and outcome assessments. They have preknowledge of the project from participating in the development of the intervention, and will be trained over a period of 4 weeks in the assessments. The PhD student, also a therapist, will assist in the assessments and be responsible for data collection, storage and analysis. A data manager will supervise the overall organisation, storage and security of the data and ensure information is recorded accurately.

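### The unqualified statement that outcome examiners are blinded is not supported by the assessor arrangements and village-based allocation that the protocol article describes

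*Protocol article*

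**What the plan says.** Two sections of the protocol article describe who assesses the children.

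Randomisation and blinding gives one account. For baseline: "A team of therapists and a social worker will administer the assessments and surveys before the study to capture background and baseline data". For follow-up: "A group of independent therapists, not involved in the intervention, will administer the outcome measures after the interventions". It then states without qualification: "These examiners will be blinded to group allocation".

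Data collection and monitoring gives another: "Two therapists not involved in the intervention will administer the baseline and outcome assessments". Of these two it says: "They have preknowledge of the project from participating in the development of the intervention". It adds a third person: "The PhD student, also a therapist, will assist in the assessments and be responsible for data collection, storage and analysis". The blinding paragraph does not mention this person.

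On allocation, Randomisation and blinding says: "Children will thus be allocated to groups depending on the village where they reside". Neighbouring villages are grouped into two geographic areas, and a single coin flip decides which area is treated first.

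Two data sources are described for one arm only. The Goal Attainment Scale is restricted to the intervention group (Goal Attainment Scale), and a monthly care diary is requested from usual-care caregivers (Standard care arm). The caregiver-skill videos are filmed at the child's home (Caregivers' skill and behaviours). GMFM-66 is named as the primary child outcome (Gross Motor Function Measure-66).

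**The concern.** A reader of the blinding paragraph would expect GMFM-66 and the other examiner-scored measures to be rated by outsiders who do not know the arm. The later section describes raters who helped to build the programme, assisted by someone in charge of the trial's data. The geographic allocation also makes the arm readable from an ordinary fact about each family.

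What is at stake is detection bias in the between-arm comparison, chiefly at year 1. That is the one assessment at which one group has had the programme and the other has not, because the waitlist group receives it during the second year. If the results are reported as examiner-blinded on the strength of this paragraph, readers will credit the GMFM-66 result with a protection that the described arrangements do not secure.

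**Working it through.** The article gives no figure for blinding, so there is none to reproduce. The check sets the sections side by side.

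1. **Who assesses, and when.** Randomisation and blinding has a baseline team that includes a social worker, then a group of therapists at follow-up. Data collection and monitoring has two therapists at both times. The two could overlap, since the baseline team is not said to exclude the later examiners. As written, though, the sections differ on who makes up the baseline team, on whether the same people assess at both times, and on whether a PhD student takes part.

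2. **Independence.** Both sections say that the therapists take no part in the intervention. Only the second says that they helped to develop it. That conflicts with calling them independent. It is not evidence that they know which area was treated first.

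3. **The PhD student.** The student assists in the assessments and is responsible for gathering, storing and analysing the data. No data are carved out of that responsibility. The data include Goal Attainment Scale scores for intervention children only and diaries described for usual-care families only. A child's having one record or the other identifies the arm, so a person with this role cannot plausibly be blind. Organisation and management also lists "an administrative project manager, a PhD student and a parent carer" among the members of the Site Steering Committee. This is probably the same person, but the article does not say so, and the argument does not need it.

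4. **Village and arm.** With two geographic blocks and one coin flip there are 2 possible allocations for the whole trial. The planned sample is 44 + 44 = 88 children. Suppose an assessor knows which villages form each block and learns the arm of one child. The allocation of both blocks is then fixed, and so is the arm of each of the other 88 − 1 = 87 children whose village the assessor knows. In an individually randomised trial, one such disclosure would reveal one child. Here it can reveal all of them.

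5. **Outcomes exposed.** These are the measures that an examiner scores: GMFM-66, and the caregiver-skill videos if the scorer can recognise the place or is told the arm.

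6. **Size.** Let s_I and s_C be the mean scoring shifts in the intervention and usual-care arms. The expected observed difference is the true difference + (s_I − s_C). Knowledge of arm matters only if it makes s_I and s_C differ. The documents give no input for either term, so no number can be attached.

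**The case against.** The strongest reply is that nothing in the article says any examiner is told the allocation. Both sections keep the assessors out of the intervention, and prior knowledge of a project is not knowledge of a coin flip. Assisting in assessments need not mean scoring GMFM-66 at follow-up. The article is also a condensed account, and masking procedures may be set out in the full protocol.

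Much of this stands. It rules out saying that the two therapists are shown to be unblinded, and it means that the absence of masking detail is not itself the fault. It does not remove the conflict between the two sections, the unmentioned role of the PhD student, or the fact that village determines arm.

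Five stronger readings are tempting, and the documents do not support them:

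- *Different teams at baseline and follow-up would bias the comparison.* If each team sees all children, the average shift is common to both arms and cancels in the planned between-group difference.
- *Assistive devices give the arm away.* Standard care arm says that usual-care children may receive donated wheelchairs or crutches, so a device alone does not identify the arm.
- *Caregiver-reported outcomes are wrongly presented as blinded.* The claim covers examiners only. No section says that caregivers are blinded, and the Pediatric Evaluation of Disability Inventory is openly described as reported by parents.
- *The false effect can be put at a given number of points.* Any such number would be only an illustration.
- *Assessment must move to a common site.* The article does not say where GMFM-66 is done, and the cost of such a move to families cannot be judged from it.

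**Conclusion.** The concern holds in limited form. The statement that examiners are blinded claims a property that the described design does not securely have. It is not supported, as an unqualified claim, for examiner-scored outcomes, including the primary child outcome.

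The firmest parts are textual: the two sections disagree on who assesses, and therapists who helped to develop the programme are called independent. The PhD student's lack of blinding is a strong inference. It assumes that responsibility for the data includes the arm-specific records. Disclosure through village is a risk. It assumes that assessors learn where children live and which area was treated first.

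A reader might infer that blinding is known to have failed, or that the GMFM-66 comparison will be biased in favour of the programme. The documents establish neither, and neither the size nor the direction of any bias can be derived from them. The matter should be corrected before outcome assessment, but it does not invalidate the design.

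**What to change.** - Reconcile Randomisation and blinding with Data collection and monitoring into one rule that states who assesses at baseline, year 1 and year 2.
- Drop the word independent for therapists who helped to develop the programme. Say instead that they do not deliver it.
- Exclude the PhD student from administering or scoring examiner-rated outcomes after baseline.
- Have assessors work from study ID, with village and programme exposure withheld where feasible.
- Score the caregiver videos in random order, without arm or time point. Ethics already provides for de-identified video file names.
- Record each assessor's guess of the child's arm, so that the success of blinding can be reported.
- Restate the claim as blinding intended for examiner-scored outcomes only, and report it as not assured where village or setting reveals the arm.

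The cost is modest scheduling work with existing staff and a less favourable blinding statement. These steps reduce the risk but cannot remove it, because village still determines arm. That is why the claim needs to be qualified as well.
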